#### Control group

As we are interested in investigating the effect of COS-P as an add on to the usual treatment, both the intervention group and the control group will receive treatment as usual (TAU) at the clinic and/or in the community. TAU consists of clinical assessment and treatment and is not under the control of trial investigators. Clinical assessment might include intelligence tests, cognitive testing, school observations and parent and teacher questionnaires. TAU could involve psychoeducation, advising parents and in some cases medical treatment. Parallel to the trial, the participating children will undergo regular treatment procedures at the clinic and/or in the community. Possible medical treatment is decided by the parents and the treating specialist, who is unrelated to the trial. Families, who have children in medical treatment, are asked not to change the child’s medication dose during the ten weeks of the intervention. No other treatments are prohibited, but parents are encouraged not to participate in parent training treatments during the trial. Additionally we register all treatments that participants receive during the trial period, including TAU at all sites. Control group participants have the possibility to participate in the COS-P after 6 months in order to minimize attrition.

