#### Intervention group

In addition to TAU that children in both groups receive, parents of children in the intervention group will participate in 10 manualized COS-P sessions. Although the original COS-P consists of 8 sessions, we choose to add two more sessions allowing more time for in depth discussion. Each of the sessions have a 2-hour duration and are conducted at the clinic by two COS-P-certified therapists. Treatment groups consist of 4–5 families. If parents miss a session, they are offered an 30-minutes make-up session.

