## Statistical plan and data analysis

### Sample size and power analysis

We are planning a trial of a continuous response variable Coding Interactive Behavior from independent control and experimental participants allocated at a 2:1 ratio.

Based on a meta-analysis of attachment-based interventions [71] we expect a standardized effect size of *d* = 0.44 for comparing the change in maternal sensitivity from baseline to follow-up between the intervention group and the control group. Using significance level of 5% and power of 80%, and with a 2:1 randomization ratio, 124 participants in the intervention group and 62 in the control group are needed (total *N* = 186).

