### Analytical model

For the intent to treat analysis of the primary, secondary and explorative outcomes, regression analysis and /or ANOVA will be used. For not normally distributed data, robust standard errors, truncation or transformation will be used. For missing data, the direct maximum likelihood method (full information likelihood) or multiple imputations will be used. In addition, per protocol analyses will be conducted for patients completing at least seven sessions, using regression analysis and /or ANOVA with robust standard errors, truncation or transformation when needed.

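### The additional per-protocol analysis is defined by attendance that only the COS-P arm can show before T1, so it leaves either no controls or a contrast that randomisation no longer protects

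*Protocol article*

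**What the plan says.** The Analytical model section puts intention to treat first: "For the intent to treat analysis of the primary, secondary and explorative outcomes, regression analysis and /or ANOVA will be used". It then adds that "per protocol analyses will be conducted for patients completing at least seven sessions". The methods for this second analysis are again regression and/or ANOVA, with robust standard errors, truncation or transformation when needed. The section gives no rule for which controls enter this set.

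Sessions exist in one arm. Under Intervention group, "parents of children in the intervention group will participate in 10 manualized COS-P sessions", so the threshold is 7/10 = 70% of what is offered. The same section adds: "If parents miss a session, they are offered an 30-minutes make-up session". It does not say whether a make-up counts towards the seven.

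Under Control group, families receive treatment as usual: "TAU consists of clinical assessment and treatment and is not under the control of trial investigators". Later access is possible: "Control group participants have the possibility to participate in the COS-P after 6 months in order to minimize attrition". The starting point of those 6 months is not given. According to Time points, T1 falls within 2 weeks of the end of the intervention and T2 falls 6 months after it ends.

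**The concern.** A per-protocol set should be defined by something that either arm can satisfy or fail. Here the criterion is attendance at sessions that controls are not offered before T1. Removing low attenders from one arm leaves families selected by their own behaviour after randomisation. The comparison group still contains the families who would have attended poorly had they been offered COS-P.

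The article gives reason to think such selection could matter. Hypothesis and aim of the study names parental attachment style, psychopathology and depressive symptoms as possible moderators and predictors of outcome. It is an assumption, though a reasonable one, that these traits also affect attendance at 2-hour group sessions. The listed methods (robust errors, truncation, transformation) deal with the shape of the data, not with selection on attendance.

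What is at stake is interpretation. A per-protocol estimate is easily read as the effect of COS-P when it is received, whereas this one would mix that effect with differences between attenders and non-attenders.

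**Working it through.** **1. The plan's own figure.** Under Sample size and power analysis, "we expect a standardized effect size of" d = 0.44 for the between-group difference in change, at 5% significance, 80% power and 2:1 allocation. Taking the test as two-sided, the normal approximation gives controls = (1 + 1/2) × (1.960 + 0.842)² / 0.44² = 1.5 × 7.85 / 0.1936 = 60.8, rounded up to 61, total 183. The noncentral t-test gives 79.7% power with 61 controls and 80.3% with 62. So 62 + 124 = 186 reproduces. The point concerns the analysis set, not the sample size.

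**2. The two readings of the rule at T1.**
- *Literal:* no control has completed seven sessions, so there is no between-arm comparison.
- *Workable:* COS-P families with at least seven sessions against all controls. Step 3 examines this reading.

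**3. Bias of the workable reading.** Let c be the completion share in the COS-P arm. Let g be the difference, in SD of change, between completers and non-completers had neither received COS-P. By randomisation, the mean untreated change of the controls equals that of the whole COS-P arm, which lies (1 − c) × g below that of the completers. Hence

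attenders minus controls = effect in completers + (1 − c) × g.

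The document gives neither c nor g, so both are assumed:

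| c | g | bias (SD) | share of 0.44 |
|---|---|---|---|
| 0.7 | 0.3 | 0.3 × 0.3 = 0.09 | 20% |
| 0.7 | 0.5 | 0.3 × 0.5 = 0.15 | 34% |
| 0.8 | 0.3 | 0.2 × 0.3 = 0.06 | 14% |
| 0.8 | 0.5 | 0.2 × 0.5 = 0.10 | 23% |
| any | 0 | 0 | 0% |

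A negative g gives the same sizes with the opposite sign. Because d = 0.44 refers to change, g must be a gap in untreated *change*. A stable baseline difference that cancels in the change score does not count. If the model adjusts for covariates, g is the gap that remains after adjustment.

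**4. A second model as a check.** Suppose attendance follows a latent propensity with correlation rho to the outcome. The top share p of the 124 is kept with all 62 controls, and the true effect is zero. The bias is rho × phi(k)/p, with k = Phi⁻¹(1 − p).

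| p | kept | rho | spurious d | two-sided rejection |
|---|---|---|---|---|
| 0.7 | 87 | 0 | 0 | 5.0% |
| 0.7 | 87 | 0.1 | 0.05 | 6.0% |
| 0.7 | 87 | 0.2 | 0.10 | 9.2% |
| 0.7 | 87 | 0.3 | 0.15 | 14.8% |
| 0.6 | 74 | 0.3 | 0.19 | 20.6% |
| 0.9 | 112 | 0.3 | 0.06 | 6.6% |

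The two models agree. At p = 0.7, rho = 0.2 and 0.3 correspond to g = 0.099/0.3 = 0.33 and 0.149/0.3 = 0.50.

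**5. What a complier-average analysis would cost.** Its standard error is roughly the intention-to-treat standard error divided by the share exposed. With full follow-up and SD = 1, the intention-to-treat value is √(1/62 + 1/124) = 0.156. Dividing by 0.8 gives 0.194, and dividing by 0.7 gives 0.222.

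**6. Why the seven-session cut-off should not be the main exposure.** Let q be the share attending 1-6 sessions, e6 their effect and e7 the effect in completers. The intention-to-treat effect is c × e7 + q × e6. Dividing by c gives e7 + (q/c) × e6, which equals e7 only if 1-6 sessions do nothing or nobody falls in that range.

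**The case against.** **The comparator is inferred.** A reader might take it as stated that attenders are compared with unselected controls. The article does not say so, and comparators or adjustment for a secondary set may be laid down in a full protocol or SAP that is not shown. This stands as a limit on wording. It does not remove the point, because the article itself fixes the threshold, and the threshold counts something that only one arm can do before T1.

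**Bias is not certain, and its direction is unknown.** A reader might infer that the analysis is biased in favour of COS-P by design. The document does not support that. Bias needs a link between attendance and outcome, and none is reported. Families under more strain could attend more. The COS-I section of the Introduction describes an uncontrolled study in which those with borderline or clinical symptoms improved most. At 90% attendance the bias is small even with rho = 0.3. This objection stands.

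**The randomised analysis is kept.** A reader might infer that the per-protocol result could rescue a null finding. Intention to treat covers all outcomes, the per-protocol analysis is introduced only as an addition, and its threshold is set in advance. Nothing suggests that it could override the main result. This stands too and limits how much weight the point carries.

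**The alternative has weaknesses of its own.** A binary seven-session exposure breaks the exclusion restriction if fewer sessions act, and a session-count exposure assumes a linear dose effect. Both are true, so the choice of exposure matters.

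**Controls' inability to meet the rule is certain only at T1.** Depending on where the 6 months start, some controls might take up COS-P before T2. This is correct, and it complicates the planned rule and any alternative alike.

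**Conclusion.** The point holds in a limited form. The additional per-protocol analysis rests on a criterion that controls cannot meet before T1. It therefore yields either no comparison or one that randomisation does not protect, and the listed methods do not address the selection. The intention-to-treat analysis is unaffected.

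The size is illustrative only: 0.06-0.15 SD, or 14-34% of the planned 0.44, if 70-80% complete and the gap in untreated change is 0.3-0.5 SD. It is zero if attendance is unrelated to outcome, and the sign follows that of the relation. These figures assume that all controls enter the comparison and that no adjustment closes the gap. The document supports neither a definite bias nor a direction. What it does support is a cheap improvement to a supplementary analysis.

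**What to change.** Keep intention to treat as the main analysis. To estimate the effect of receiving COS-P, specify a complier-average causal effect analysis on all randomised families:

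- Use randomised arm as the instrument (for example by two-stage least squares), with the same covariates and error structure as the final intention-to-treat model.
- Take number of sessions attended, or any attendance, as the main exposure. Run the version with at least seven sessions as a sensitivity analysis, because 1-6 sessions may also act.
- Define attendance so that it is clear how make-up sessions count.
- Record any uptake of COS-P by controls before T2 and enter it as exposure at T2.
- Label any attender-only comparison as descriptive and state which controls it uses.

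The cost is wording in the analysis plan, since the current rule already needs attendance data. Recording control uptake is a small addition. The statistical price is a wider interval: the standard error is about 1/0.8 = 1.25 to 1/0.7 = 1.43 times the intention-to-treat value if 70-80% count as exposed, and less if more do. The assumptions must be stated. Allocation must act only through attendance, which is harder to defend for questionnaires completed by unblinded parents than for the blinded video ratings. The session-count version also assumes a linear dose effect.

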## Discussion

Considering the meta-analytic evidence on associations between the quality of attachment, psychopathology and the social functioning of the child, it is important to investigate if an attachment-based intervention could enrich the current child psychiatric treatment. Research is emphasizing the essential impact of the quality of the parent-child relationship on the child’s wellbeing. Therefore it is important to target parental sensitivity in interventions and to investigate its impact on the psychiatric symptoms of the child. Today, there is a general lack of interventions aiming to improve parental sensitivity and attachment security in populations of children referred to treatment in child psychiatry. This randomized, controlled trial with clinically referred children to mental health services will produce new and important knowledge regarding if parent training can improve parental sensitivity and children’s psychiatric symptoms. It is essential to investigate if child psychiatric treatment can benefit from interventions targeting the parent-child relationship. Ideally, children referred to psychiatric services and their parents may benefit from the intervention by improving parental sensitivity and decreasing the symptom load of the child as well as reducing parental stress. Helping parents to become more responsive to their children’s emotional needs and improving their relational capacity, could possibly impact on their children’s current psychiatric symptoms. Especially young children with emotional and behavioral symptoms are often not offered treatment within the current Danish psychiatric system because of their unspecific symptoms. If the intervention shows significant positive results, the COS-P could be easily implemented both at the psychiatric child clinics and in community settings. This would make it possible for many families to access help at an early stage and potentially prevent the development of more severe psychopathology in children, thereby improving their overall mental health and reducing adverse outcomes associated with mental health problems.

### Trial status

Trial registration: ClinicalTrials.gov Identifier, registered on July 5, 2018.

Protocol version 3, date 11.11.2020. The first participant was enrolled August 15th, 2018. Recruitment is currently ongoing till 2023. Currently 64 participants have been randomized. Recruitment of the trial has been impacted by the ongoing Covid-19 pandemic, slowing down recruitment as group interventions were not allowed for a longer period of time. Additional details about the trial registration are presented in Table 1.

**Table 1 pone.0265676.t001:** Trial registration data set.

Data category	Information^32^
Primary registry and trial identifying number	ClinicalTrials.gov
	NCT03578016
Date of registration in primary registry	July 5th, 2018
Secondary identifying numbers	17/7474; S-20170032
Source(s) of monetary or material support	Psychiatric Research Foundation in Region of Southern Denmark, A.P. Møller Foundation, Jascha Foundation
Primary sponsor	Psychiatric Research Foundation in Region of Southern Denmark
Secondary sponsor(s)	Jascha Foundation, A.P. Møller Foundation
Contact for public queries	[name] e-mail: [contact]
Contact for scientific queries	[name] e-mail: [contact]
	University of Southern Denmark, Odense, Denmark
Scientific title	Protocol for a randomized controlled trial comparing the Circle of Security-parenting (COS-P) with treatment as usual in child mental health services
Countries of recruitment	Denmark
Health condition(s) or problem(s) studied	Oppositional behavior, child psychiatric symptoms
Intervention(s)	Active comparator: Circle of Security-Parenting (COS-P), a group treatment for families
	Control group: Treatment as usual (TAU)
Key inclusion and exclusion criteria	Ages eligible for study: 3–8 years
	Sexes eligible for study: both
	Accepts healthy volunteers: no
	Inclusion criteria: Children, referred to mental health services who score ≥ the 93d percentile on CBCL total score and the ODD or conduct disorder subscale; age between 3–8 years, both inclusive; informed consent from all legal guardians
	Exclusion criteria: *Children*: autism spectrum disorder, serious psychopathology requiring immediate clinical attention (e.g. suicidality, psychotic symptoms); head injury or verified neurological disease; intelligence quotient (IQ) less than 80; a medical condition requiring treatment, and/or a lack of informed consent from their custodians.
	*Parents*: a known diagnosis of schizophrenia, known substance abuse and/or severe intellectual impairment.
Study type	Interventional
	Allocation: randomized intervention model. 2:1 assignment masking: investigator and outcomes assessor are blinded.
	Primary purpose: treatment
	Phase III
Date of first enrolment	August 15th, 2018.
Estimated primary completion date	December 2023
Estimated study completion date	2024
Target sample size	186
Recruitment status	Recruiting
Primary outcome(s)	Coding Interactive Behavior (CIB): parental sensitivity
Key secondary outcomes	1. Maternal Intrusiveness: (CIB)
	2. Limit Setting (CIB)
	3. Dyadic reciprocity (CIB)
	4. Negative states (CIB)
	5. Child Behaviour Check List (CBCL)-externalized
	6. CBCL-: internalized symptoms
	7. Eyberg Child Behaviour Inventory (ECBI)
	8. Berkeley Puppet Child interview
	9. Coping with children’s negative emotions scale
	10. Parenting Stress Scale
	11. SDQ
